### Objectives

This paper describes the protocol of a pragmatic randomized controlled trial (RCT), PAC-WOMAN, targeting Portuguese post-menopausal women diagnosed with hormone-receptor-positive breast cancer, currently on Aromatase Inhibitors. This project primary aims are:a) To develop and test the long-term (16-month) effectiveness and cost-effectiveness of two 4-month group-based interventions, compared to a control waiting list, on promoting sustained changes in PA, sedentary behavior, QoL, and healthcare services’ use (primary outcomes)b) To compare the effects of both interventions (i.e., brief PA counseling vs. structured exercise) on long-term changes in our primary outcomes, as well as their cost-effectivenessc) Evaluate pretreatment moderators of 4-month and 16-month changes in PA, sedentary behavior, and QoLd) Identify critical motivational (theoretical) mechanisms of change in PA, sedentary behavior, and QoL, and explore their mediating role.

As secondary aims, we will study the impact of both interventions on AI therapy continuation, adverse events of treatment, disease-free survival, body composition, sleep quality, physical parameters (e.g., muscular strength), and psychosocial factors (e.g., body image). Furthermore, process evaluation will also be conducted seeking to analyze implementation facilitators and barriers.

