#### Rationale for the PAC-WOMAN trial

Supervised exercise programs may provide significant symptomatic benefit for patients living with or beyond cancer [11, 12], however their widespread implementation may be restricted by lack of facilities and funding. Indeed, there is a lack of effective PA interventions that are low-cost and can be implemented at scale and fully-embedded in a system [37]. Furthermore, once these exercise programs end, the sustainability of PA behavior and its subsequent health outcomes may be at risk. Thus, there is a need for effective, scalable, low-cost interventions to enhance the adoption and maintenance of regular PA. Brief counseling interventions that promote autonomous motivation for free-living PA, reinforcing self-regulation resources, may be an alternative, less expensive, solution. Evidence has suggested that brief counseling interventions may be as effective as more intensive interventions [38].

Indeed, there is an urgent need for affordable and practical interventions that can be delivered in real-world health care or community settings and have similar degrees of effectiveness [34]. A systematic review exploring differences between supervised exercise, home‐based exercise, and walking advice for intermittent claudication has not found clear differences in quality of life or self‐reported functional impairment between supervised exercise and free-living PA solutions, suggesting that the latter might also be important alternatives within PA promotion [39]. In line with this, brief PA counseling interventions, that are underpinned by theoretical models of behavior change and incorporate behavior change techniques, such as identifying barriers, self-monitoring, goal setting, and feedback provision, have been shown to increase PA in the general population [40, 41], as well in people with physical disabilities [42].

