In sum, existing interventions targeting supervised exercise, although very effective in promoting short-term health outcomes [43], may be labor intensive and costly for staff and participants. Also, long term effects, once the intervention is finished, may be jeopardized given that supervised interventions may have the detrimental effect of patients’ internalization of the message that their condition is to be dealt with by procedures and techniques essentially under the responsibility and “steering” of an external expert (e.g., simply follow an exercise prescription), thus promoting an external locus of causality. In contrast, theory-based, evidence-informed brief counseling, delivered in a manner that reduces dependence on staff and facilitates self-regulatory skills, could alleviate time and financial barriers while promoting free-living, integrated into daily-life, PA/exercise. From a self-determination theory (SDT) perspective [28], lasting behavior change does not depend on complying with external demands for change but rather on accepting the regulation of change as one’s own. This requires internalizing the regulation of relevant behaviors and integrating them with one’s sense of self and one’s values and goals, so they can become the basis of autonomous regulation [27].

Thus, the PAC-WOMAN trial will test effectiveness and cost-effectiveness of these 2 types of interventions (supervised structured exercise vs. brief theory-based PA counseling) against a waiting-list, standard care, control group. This is of importance given that although an improved health profile (e.g., lower blood pressure, lower body mass index, improved tumoral biomarkers, cardiorespiratory fitness, physical function) is expected as a short-term result of the exercise intervention, the maintenance of the PA/exercise habits after the end of the intervention remains to be determined (and consequently its long-term health outcomes). On the other hand, will a brief motivational (SDT-based) intervention (lighter in time and resources) be enough to trigger a more physically active lifestyle? And will the potential behavioral, motivational, and self-regulatory changes endure in the long term? (With a sufficient magnitude to produce positive health outcomes?).

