A cost-effectiveness analysis will be conducted, from the NHS and societal perspectives, in comparison with the “no intervention” arm. The time horizon of the study will coincide with that of the intervention follow-up, so that no specific modeling tools will be used. Quality-adjusted life years (QALYs) will be estimated using EORTC QLQ-C30 collected during the intervention, mapped to EQ-5D using mapping algorithms from the literature [97]. Intervention costs will be estimated using a bottom-up approach [99]. Attendance to PA counseling and exercise sessions will be registered; exercise physiologists’ time-related costs will be estimated using their gross hourly salaries, and equipment and disposables’ costs through invoices. Healthcare resources will include consultations, drugs, tests and exams, in-patient stays and day care sessions, valued using usual official tariffs. Absenteeism will be assessed using participants’ reports of their number of absence days or percentage of normal working hours worked, valued at patients’ hourly wage. The incremental cost-effectiveness ratio (ICER) will be calculated as the difference in costs divided by the difference in QALYs between intervention and control groups.

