To the best of our knowledge, PAC-WOMAN is the first study using Self-Determination Theory as a way of promoting the sustained adoption of an active lifestyle among cancer survivors, by offering a person-centered approach that fosters individuals’ sense of autonomy, competence and relatedness and explores meaningful links between PA and patients’ values and life aspirations, at the same time it stimulates the acquisition of validated self-regulatory skills (e.g., self-monitoring, goal setting or action planning). The significance of the PAC-WOMAN study is further supported by its focus on long-term adherence, along with the investigation of motivational mechanisms mediating changes in PA, sedentary behavior, and quality of life and of putative moderators explaining to whom these two interventions might work best. Finally, PAC-WOMAN is the first RCT study testing the long-term effectiveness and cost-effectiveness of a more traditional exercise program vs. a brief theory-based PA motivational counseling (against a control group). This is of importance given that although a larger improvement in health/fitness outcomes is expected as a short-term result of the exercise intervention, the maintenance of PA/exercise habits in the long term remains to be determined. On the other hand, will a brief motivational (SDT-based) intervention, lighter in time and resources, be enough to induce behavioral, motivational, and self-regulatory changes, and trigger a more physically active lifestyle?

This study is expected to have an immediate benefit to enrolled breast cancer survivors, and a direct impact on the improvement of interventions designed to promote adherence to active lifestyle behaviors. Dissemination of project-related interventions into the community, using community resources in close collaboration with the health care service, will provide much-needed cancer survival management tools that empower patients to maintain health-behavior changes for life, in a familiar social (non-medical) environment. If successful, this study will contribute to a decrease in NHS healthcare use, liberating resources for other needs.

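### The cost-effectiveness analysis is written only against the control arm, so primary aim b (counselling versus structured exercise) has no matching economic comparison

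*Protocol article*

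**What the plan says.** Objectives lists four primary aims. Aim a covers the "effectiveness and cost-effectiveness of two 4-month group-based interventions, compared to a control waiting list". Aim b is separate: it compares brief PA counselling (PAC) with structured exercise (StEx) on the primary outcomes and on cost-effectiveness.

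The rest of the article treats this contrast as central. The Rationale says that supervised exercise "may be labor intensive and costly for staff and participants" and that brief counselling "may be an alternative, less expensive, solution". The Discussion presents as new the testing of the "cost-effectiveness of a more traditional exercise program vs. a brief theory-based PA motivational counseling (against a control group").

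The economic analysis is described once, in Statistical methods. The text reads "A cost-effectiveness analysis will be conducted, from the NHS and societal perspectives, in comparison with the" no-intervention arm, and the ICER is "calculated as the difference in costs divided by the difference in QALYs between intervention and control groups". No PAC versus StEx cost difference, QALY difference, ICER, net benefit or ranking of the three options appears anywhere in the article.

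**The concern.** A primary aim has no economic analysis attached to it. A funder choosing between PAC, StEx and neither can adopt only one for a given patient. The costlier programme then has to be judged by what it adds over the cheaper one, not only by what it adds over nothing. Two ratios against a common control do not carry that information. A reader who checks each ratio against a threshold, or who picks the lower ratio, may choose the programme with the smaller net benefit. The question at stake is the one on which the Rationale builds the trial: whether the lighter programme is enough, or whether supervised exercise is worth its extra cost.

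**Working it through.** **Step 1: aims against analysis.**

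| Aim (Objectives) | Contrast needed | Contrast stated (Statistical methods) |
|---|---|---|
| a | PAC vs control, StEx vs control | Yes |
| b | StEx vs PAC | None |

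The article states no cost-effectiveness figure, so there is none to reproduce.

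**Step 2: is a cost gap plausible?** From Interventions, PAC contact time is 8 × 120 min = 16 h and StEx contact time is 32 × 90 min = 48 h, three times as much. The article itself expects PAC to be cheaper. The incremental question is therefore real.

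**Step 3: what two control-based ICERs can hide.** All costs, QALY gains and the threshold below are assumed, because the article gives none. Relative to control, PAC costs +200 and gains +0.02 QALY; StEx costs +600 and its gain E is varied. The threshold is 30,000 per QALY.

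- ICER vs control = cost difference / QALY difference. For PAC: 200 / 0.02 = 10,000.
- StEx vs PAC = (600 − 200) / (E − 0.02).
- Net benefit vs control = 30,000 × QALY gain − cost. For PAC: 600 − 200 = 400.

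| StEx gain E | StEx vs control | StEx vs PAC | StEx net benefit (PAC: 400) | Larger net benefit |
|---|---|---|---|---|
| 0.018 | 33,333 | dominated by PAC | 540 − 600 = −60 | PAC |
| 0.025 | 24,000 | 400 / 0.005 = 80,000 | 750 − 600 = 150 | PAC |
| 0.03 | 20,000 | 400 / 0.01 = 40,000 | 900 − 600 = 300 | PAC |
| 0.04 | 15,000 | 400 / 0.02 = 20,000 | 1,200 − 600 = 600 | StEx |
| 0.06 | 10,000 | 400 / 0.04 = 10,000 | 1,800 − 600 = 1,200 | StEx |
| 0.07 | 8,571 | 400 / 0.05 = 8,000 | 2,100 − 600 = 1,500 | StEx |

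- At E = 0.03 both programmes pass against control. Taking the more effective one that passes would select StEx, although PAC has the larger net benefit.
- At E = 0.04 the lower control-based ICER belongs to PAC. Taking it would select PAC, although StEx has the larger net benefit.

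**Step 4: the pair of ratios does not determine the answer.** Start from E = 0.03, where the ratios are 10,000 and 20,000. Doubling both StEx increments (cost 1,200, gain 0.06) leaves StEx vs control at 20,000. StEx vs PAC becomes (1,200 − 200) / (0.06 − 0.02) = 25,000, now under the threshold. The StEx net benefit becomes 1,800 − 1,200 = 600 against 400. The same two published ratios thus fit opposite decisions.

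**The case against.** The strongest defence is that this is a condensed article and that an economic analysis plan may contain the missing contrast. That would answer an omission. Here, however, the text names a comparator and defines the ICER, and both fit aim a only. Methods for uncertainty, such as bootstrapping or acceptability curves, can properly be left to a later plan, and their absence is not part of this point.

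A second defence is that the data can answer aim b. This stands. Costs and QALYs are planned for every arm, and the StEx versus PAC increments are the differences between the two control-based increments. A reader might infer that the trial is unable to answer aim b, but the documents do not support that. Only the analysis as written falls short, because it commits to ratios from which the increments cannot be recovered.

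A reader might also infer that control-based ICERs systematically flatter StEx. They do not: in the illustration the error runs towards StEx at a gain of 0.03 and towards PAC at 0.04. At 0.07 the control-based figure for StEx (8,571) is even less favourable than its figure against PAC (8,000).

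Finally, a reader might infer that the societal perspective wrongly leaves out participants' time and travel, given the 48 h versus 16 h of sessions. The listed cost items are not said to be exhaustive. The gap in session hours assumes full attendance and ignores the exercise that PAC participants are encouraged to do on their own. Travel data would also be a new collection after 68 women had been randomized (Trial status). That criticism is not made here.

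**Conclusion.** The mismatch is established from the text alone: aim b asks for a PAC versus StEx economic comparison, and Statistical methods states comparisons with control only. It should be corrected before the economic analysis, but it does not threaten the design or the data.

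The consequence is a possibility, not a measured bias. Under the assumed inputs, StEx versus PAC runs from dominated to 8,000 per QALY as the StEx gain goes from 0.018 to 0.07 QALY. The preferred programme at 30,000 changes between gains of 0.03 and 0.04. It also depends on the threshold: at a gain of 0.04 the two programmes tie at 20,000 (net benefit 200 each), and PAC leads at 15,000 (100 versus 0). Other costs would move these points. What does not depend on the assumed values is that two ratios against a common control do not rank the two programmes.

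**What to change.** Amend the cost-effectiveness paragraph in Statistical methods:

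- Keep each intervention versus control, labelled as the analysis for aim a.
- For aim b, state a full incremental analysis of the three arms: order them by mean cost, remove dominated and extended-dominated options, and calculate ICERs between successive remaining options.
- Report the StEx versus PAC cost difference, QALY difference, and ICER or net monetary benefit, with its uncertainty, whatever the ordering turns out to be. Estimate that uncertainty from the participant-level data, since the two control-based comparisons share an arm and are correlated.

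The choice of threshold and of uncertainty method can go in the analysis plan. The cost is a few sentences and one further contrast on costs and QALYs already planned for all arms. No new data, visits or participants are needed, and the cohorts already randomized are unaffected.

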#### Participants

Recruitment (ongoing) will aim for 122 Portuguese breast cancer survivors who have completed primary cancer treatment and are currently under aromatase inhibitors therapy and will subsequently be randomized to receive the brief PA counseling (PAC), the structured exercise program (StEx), or to a waiting list control group.

The inclusion criteria for entering this study are: 1) post-menopausal women, below 70 years old; 2) histologically confirmed hormone-receptor-positive breast cancer (stage I, II, III); 3) having initiated AI hormonal therapy following the primary treatment (surgery, radiotherapy, chemotherapy, etc.), at least 1 month before being enrolled; and 4) ECOG-Performance Status 0–1 (being able to perform light-to-moderate physical activities). The exclusion criteria are: 1) evidence of stage IV cancer or synchronous tumors; 2) uncontrolled hypertension, cardiac or pulmonary disease; 3) contraindications to exercise training according to the assistant doctor; 4) inability to provide informed consent; and 5) expected inability to fulfill the proposed program schedule.

Given the study design, sample size estimations were calculated for primary outcomes having one-way factorial analysis of variance with repeated measures as the reference statistical analysis. Based on previous research findings, and considering a 25% dropout, the sample size was estimated in 98 participants to detect a small to moderate effect size (α = 0.05; statistical power = 0.80) using G*Power 3.1. Consensual criteria on sample size needs for mediator/moderator analyses are not consensual and depend on the procedure and number of indicators and pathways in the models; therefore, we increased the estimated number of participants in 25%, obtaining a final estimated sample size of 122 participants.

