#### Assessments

Participants will be assessed at four time points: baseline (T_0_), 4 months (intervention’s end; T_1_), and 10 and 16 months (T_2-_T_3_; during follow-up). A schematic description of all the measurements by timepoint is presented in Table 2. Assessments will take place in standardized conditions, at the exercise setting, in a calm comfortable environment, in small groups, with a group of study technicians attending every assessment period. At each assessment point, the research staff provides participants with an accelerometer, which they are required to wear for a week, and schedules an evaluation visit to the exercise setting, where participants complete the full battery of assessments, described below, and according to the assessment plan for that timepoint. An individual report with the assessment results will be provided to each participant at the end of each assessment period is complete. Participants will be contacted close to each assessment point to determine any changes in their contact or personal information that may have occurred, especially in the fulfillment of the eligibility criteria.

**Table 2 Tab2:** Measurements’ timeline

	**Intervention**		**Follow-up**	
	**T0 Baseline**	**T1 4 months**	**T2 10 months**	**T3 16 months**

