**Primary outcomes**				
Physical activity/sedentary behavior (objective and self-reported)	X	X	X	X
Lifestyle physically active choices	X	X	X	X
Quality of Life	X	X	X	X
Healthcare use	-	X ^a^	-	-

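### The ICER's QALY difference is defined with no stated adjustment for baseline utility, although the trial collects it; this leaves chance imbalance in the estimate and gives up precision

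*Protocol article*

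**What the plan says.** Cost-effectiveness belongs to the primary aims. Under Objectives, the first aim is "To develop and test the long-term (16-month) effectiveness and cost-effectiveness of two 4-month group-based interventions, compared to a control waiting list", and the second aim compares the two programmes on the same footing.

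The economic method is one paragraph under Statistical methods. On utilities: "Quality-adjusted life years (QALYs) will be estimated using EORTC QLQ-C30 collected during the intervention, mapped to EQ-5D using mapping algorithms from the literature". On the horizon: "The time horizon of the study will coincide with that of the intervention follow-up". On the estimate: "The incremental cost-effectiveness ratio (ICER) will be calculated as the difference in costs divided by the difference in QALYs between intervention and control groups". Nothing in that paragraph mentions baseline utility or any covariate.

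Three other places bear on the point:

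- Earlier in Statistical methods, adjustment for potential covariates (primary treatment and length of AI therapy are the examples) is stated for the ANOVAs of the primary and secondary outcomes. It is not extended to QALYs.
- The list under Potential covariates is demographic, medical and dietary. It does not include baseline utility.
- Table 2 shows quality of life measured at all four visits, T0 included: "Quality of Life X X X X".

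**The concern.** A QALY total is normally the area under a woman's utility curve. T0 utility is one point on that curve, and later utilities tend to correlate with it. A woman who starts high therefore tends to accumulate more QALYs in any arm. Unlike a change score or a time-by-arm contrast, a plain difference in mean QALYs does not remove a T0 difference that arose by chance.

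With 122 women in three arms, some imbalance in T0 utility is to be expected. Left in the estimate, it appears as part of the QALY gain or loss credited to a programme. The variation between women that T0 utility could have explained also stays in the error term. Both affect the denominator of a ratio that answers a primary aim, and the measurement needed to deal with them is already in the visit schedule.

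**Working it through.** **Sample size as stated.** The Participants section reaches 98 and adds 25%: 98 × 1.25 = 122.5, given as 122, so the figure reproduces. With equal allocation (an assumption, since no ratio is stated) that is 122/3 = 40.7 per arm. After the 25% dropout it is 40.7 × 0.75 = 30.5, about 30 completers. The percentage reductions below do not depend on these counts.

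**Inputs.**
- From Assessments and Table 2: visits at 0, 4, 10 and 16 months, with quality of life at each.
- Assumed: trapezoidal area under the curve over all four visits; the same utility SD, s, at each visit; the same correlation ρ between any two visits. The protocol gives neither s nor ρ, so ρ is taken as 0.3, 0.5 and 0.7.

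**Trapezoid weights.** The intervals are 4, 6 and 6 months, so the weights are w = (2, 5, 6, 3)/12 years, which sum to 16/12 = 1.333. The sum of squares is 74/144 = 0.514, and the square of the sum is 1.778.

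**Formulas.**
- Var(QALY)/s² = (1 − ρ) × 0.514 + ρ × 1.778
- Slope of QALY on T0 utility: b = 1/6 + ρ × 7/6
- Share of QALY variance explained by T0: R² = b² / [Var(QALY)/s²]
- Reduction in the SE of the arm difference: 1 − √(1 − R²)

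| ρ | Var(QALY)/s² | b | R² | SE reduction |
|---|---|---|---|---|
| 0.3 | 0.893 | 0.517 | 0.30 | 16% |
| 0.5 | 1.146 | 0.750 | 0.49 | 29% |
| 0.7 | 1.399 | 0.983 | 0.69 | 44% |

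**On the QALY scale.** Assume s = 0.20, ρ = 0.5 and 30 per arm.
- Unadjusted SE = 0.20 × √(2/30) × √1.146 = 0.055.
- Adjusted SE = 0.055 × √(1 − 0.49) = 0.039.
- One SE of T0 imbalance = 0.20 × √(2/30) = 0.052 utility, which moves the QALY difference by 0.052 × 0.75 = 0.039.
- Check: 0.039² + 0.039² ≈ 0.055². Adjustment removes the first component and leaves the second.

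**Sensitivity to the assumptions.**
- If correlation fades with time apart, the gain is smaller. With 0.7 between adjacent visits, then 0.7² = 0.49 and 0.7³ = 0.343, b = 0.789, Var(QALY)/s² = 1.290, R² = 0.789²/1.290 = 0.48 and the reduction is 28% rather than 44%.
- The utility sentence speaks of data collected during the intervention. If only T0 and T1 were used, the weights would be (2, 2)/12 and R² = (1 + ρ)/2 = 0.65, 0.75 or 0.85. The reductions would then be 41%, 50% or 61%.

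The gain stays material in each of these cases.

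**The case against.** The best defence is that the quoted sentence is simply what an ICER is. A regression-adjusted difference is also a difference in QALYs between groups, and an article may leave the model to a fuller economic plan. Much of this stands: the text nowhere says that the difference is raw, and this is an adjustment left unstated rather than an error stated. What remains is that the same section does state covariate adjustment for the ANOVAs and does not carry it over, and that baseline utility is not among the listed covariates. Someone following the paragraph as written would compute an unadjusted difference.

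A reader might also infer stronger things that the documents do not support:

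- *That the estimate is biased.* Under randomisation it is not. The issue is chance imbalance and lost precision.
- *That T0 imbalance passes straight into the QALYs.* T0's own weight is 1/6 year. At ρ = 0.5 that is 0.167/0.75 = 22% of the shift; the rest depends on an assumed correlation with later visits.
- *That missing adjustment makes the ICER swing several-fold.* Such a swing rests on an assumed SD, correlation and true gain, none of which the protocol gives. In the example above, the residual SE after adjustment (0.039) is as large as the shift from one SE of imbalance (0.039), so ordinary sampling error would still move the ICER by a similar amount.
- *That power is lost.* The paragraph plans no hypothesis test on QALYs, so power figures do not apply.
- *That randomisation is unstratified.* The Randomization and blinding section is silent on stratification.

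**Conclusion.** The point holds as a recommended improvement in method, not as a demonstrated error. For a quantity in the primary aims, the protocol defines the QALY contrast without baseline adjustment while collecting the variable that would supply it. The benefit of adjusting is protection against chance T0 imbalance and a smaller standard error, by about 16%, 29% or 44% at correlations of 0.3, 0.5 or 0.7. These figures rest on trapezoidal QALYs over all four visits with equal variances and equal correlations. They do not depend on the utility SD, the arm size or the true effect. Adjustment will not make the ICER stable in a trial of this size; it removes one avoidable source of noise.

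**What to change.** In the cost-effectiveness paragraph of Statistical methods, state that the QALY difference is the arm coefficient from a regression of each woman's QALYs on arm and her T0 mapped utility, plus the covariates already planned for the ANOVAs. Use that adjusted difference in the ICER and in its uncertainty analysis, and report the unadjusted difference as a sensitivity result.

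State in the same place which visits enter the QALY calculation and how the area is formed, since the size of the gain depends on it. Fix this before outcome data are unblinded, so that the choice between an adjusted and an unadjusted ICER is not made after seeing both.

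The cost is a sentence or two of text and one regression, with no additional data, visits or participants.
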